#### Data Collection, Management, and Analysis

##### Data Collection

This feasibility pilot study will use a mixed methods approach using both quantitative and qualitative data.

###### Quantitative Data

These data will include digitally tracked engagement data, facilitator administrative data and self-reports on program implementation, caregiver baseline and posttest surveys, and direct assessments of children.

Digitally tracked data on parent engagement with the chatbot will be collected automatically through parent interactions with ParentText. These data will be linked to the individual participant ID. Facilitator administrative data will include a register of caregivers invited to participate in the intervention and whether they consented to participate. Facilitators will record caregiver participation in the WhatsApp support groups via the facilitator app. Information recorded will include whether caregivers sent a message (participated or did not participate) in the WhatsApp group over the week during which facilitation content messages were sent. Finally, facilitators will also complete checklists on the activities they carried out in in-person sessions and whether they shared program content on the WhatsApp support groups.

Caregiver self-completion assessments will be administered at 2 time points: baseline and after the intervention. A longer survey will be administered to primary caregivers, and a shorter version will be administered to secondary caregivers. Baseline data were collected between December 6 and 16, 2023. Postintervention data will be collected from all participants 3 weeks after the second in-person session (for participants receiving 2 in-person sessions); all other participants (those receiving only 1 in-person session) will be invited to the school to complete the assessment. All assessment data will be collected using Open Data Kit (ODK; Get ODK Inc). UPM researchers will provide assistance to caregivers with low digital literacy. Caregivers consenting to participate in ParentText but who are unable to attend the in-person session will be contacted by UPM researchers who will administer the survey over the telephone after informed consent and enter responses using ODK on tablet computers.

Direct assessments of a subsample of children (32/160, 20%) will be undertaken at baseline and after the intervention by 2 UPM researchers from the field of child development who will enter scores on the observational measure into ODK on tablet computers.

###### Qualitative Data

These data will include FGDs with caregivers, KEMAS supervisors, and KEMAS leadership team members as well as individual interviews with facilitators. All FGDs and interviews will be conducted by qualitative researchers from UPM. Participants will be asked for their consent to the discussions and interviews being audio recorded. If any participants decline, notes will be taken instead.

FGDs among caregivers will be conducted at 4 randomly selected schools, and each school will represent 1 condition. Caregivers from the selected schools will be invited to participate with other caregivers from the same school. Two FGDs for each class (1 FGD with male participants and 1 FGD with female participants) will be conducted, resulting in 8 FGDs.

In-depth interviews with 8 facilitators will be held in the 2 weeks after caregivers’ completion of the intervention. Interviews will be conducted via web-based videoconferencing.

KEMAS supervisors will participate in an FGD that will be held via web-based video conferencing. KEMAS leadership team members will also participate in an FGD that will be held via web-based videoconferencing. These 2 FGDs will be held during the week after the interviews with the teacher-facilitators.

##### Data Management

Survey data collection will be carried out through computer-assisted self-interviews using tablet computers, which will be stored in a locked cabinet at the UPM research office and accessed only by authorized personnel on data collection dates. All data collected on tablet computers and exported to ODK will be encrypted as soon as the survey is completed by the interviewer and will be accessible only to senior research personnel on a need-to-know basis. Each tablet computer will have a GPS tracking application that will permit remote deletion of stored information in the event of theft.

Paper-based surveys will be used in cases where tablet computers malfunction. These surveys will also be stored in a locked cabinet at the UPM research office. They will be destroyed once data have been transferred to ODK via tablet computers and verified for accuracy by the research team.

Quantitative data from the baseline and postintervention assessments will be anonymized and stored in a password-protected University of Oxford secure server. Data on this server will be managed by the University of Oxford central IT team and the Global Parenting Initiative (GPI) data management team, with support from the Department of Social Policy and Intervention IT office. Access, which will be managed by the GPI data management team, will be restricted to study team members or partner organizations involved in the research. Engagement data from ParentText will be stored using end-to-end encryption on the UNICEF server. Participants will be assigned a unique ID number during data collection that will enable linkage of the data across data sets.

Audio recorders will be used for in-person FGDs. Web-based FGDs and interviews will be recorded using the Google Meet audio recording function. Audio recordings from the FGDs and interviews will be transcribed verbatim and stored on password-protected devices, then securely uploaded and backed up on the University of Oxford server. Subsequently, all audio files will be deleted from the recording devices. Transcripts will be anonymized and verified, after which audio recordings will be permanently deleted from the databases.

All electronic documents will be named following a standard format, including the date as version control. Access to anonymized transcripts will be granted only by the GPI data manager via OneDrive for Business (Microsoft Corp) at the University of Oxford. Anonymized data sets will be stored securely for perpetuity and use per UK Data Archive guidance [55]. Raw data will be owned by the University of Oxford and UPM and stored by the University of Oxford. External access to the data will require approval from both principal investigators.

Data cleaning will be conducted during data collection to monitor data quality. Individual raw data sets from the baseline and postintervention evaluations will be stored separately from the final merged data set so that data reference points are available in the data validation process. All electronic documents and data, including quantitative data and transcripts of qualitative data, will be stored on at least 2 servers with access granted individually on a need-to-know basis. Thus, data will be protected from both server failure and confidentiality breaches.

##### Statistical Methods

All statistical analyses will be performed using Stata (StataCorp LLC) or R statistical software (R Foundation for Statistical Computing). Summary statistics will be used to describe all variables of interest. Descriptive analysis will be conducted to analyze recruitment, retention, adherence, and engagement data (objective 1), and all statistical tests will be 2-tailed with α=.05.

Intervention effects on primary and secondary outcomes (objective 5) will be represented by point estimates and their SEs. The main effect for each intervention component on primary and secondary outcomes will be estimated using multilevel models (including mixed models where outcomes are continuous, Poisson models where outcomes are counts or count distributed, and logistic models where outcomes are binary). Each model will specify 3 levels to account for the longitudinal and clustered nature of the data: repeated measures are nested within individuals, which are, in turn, nested within schools. Level 1 will include a term for categorical time (before and after the intervention) and for the interaction between time and intervention status; level 2 will include terms for individual sociodemographics such as age (parent and child) and gender (parent) and other individual-level covariates, centered at the sample mean; and level 3 will include terms for the intervention components and the stratifying factor. Robust SEs will be estimated to adjust for clustering. This study will report the direction and magnitude of standardized betas, incidence risk ratios, and odds ratios at a significance level of *P*<.10 with 90% CIs. Two-tailed tests will be conducted across all analyses.

Intervention costs (objective 4) will be estimated from the provider perspective. Resource inputs valued to estimate costs will include facilitator costs, such as those associated with their training to deliver ParentText (captured as their time spent attending training sessions) and with preparing and delivering specific intervention components; physical space used to deliver in-person sessions, which will be audited and valued; and travel and supplies (such as internet data and mobile phones). Local researchers and coordinators will collect resource use data in real time (ie, alongside the full study trial) via the completion of weekly ODK-based surveys. Costs related to the development of ParentText and content adaptation and translation will be included as a capital start-up cost. As the cost analyses will be conducted from the provider perspective, costs incurred by participants (travel expenditure and opportunity costs) will be excluded. While the implementing organization’s program monitoring and evaluation costs will be included in the cost estimates, broader research activity costs will be excluded. Program implementation costs and outcomes data will be recorded and analyzed in Excel. The total cost for each intervention condition will then be compared against the number of participants who completed all ParentText modules and for the positive parenting outcome.

Regarding qualitative data, the audio recordings from the interviews and FGDs will be transcribed by UPM researchers. Qualitative data will be analyzed in Bahasa Melayu using NVivo (Lumivero) and Microsoft Word using framework analysis. The analysis will include five stages: (1) familiarization, (2) the identification of themes, (3) indexing, (4) charting and summarization, and (5) interpretation and mapping. Researchers will begin by familiarizing themselves with the transcripts and identifying emerging themes. A code will then be assigned to each theme and subtheme at the indexing stage. After themes are indexed, they will be charted and summarized. Finally, interpretation and mapping will be used to develop a deeper understanding of the findings.

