#### Proximal Outcomes

##### Harsh and Abusive Parenting

Two indicators of harsh and abusive parenting (physical and emotional abuse) will be measured using items from the International Society for the Prevention of Child Abuse and Neglect Child Abuse Screening Tool–Parent version [44]. Each item measures responses on 9-point count scales, asking the number of times a behavior occurred in the previous 2 weeks (ranging from 0=0 times to 8=8 or more times).

Child physical abuse will be measured using 4 items from the physical abuse subscale that ask questions regarding the frequency of the parents disciplining their children physically (eg, “In the last 2 weeks, how often did you discipline your child by slapping, spanking, or hitting with your hand?”).

Child emotional abuse will be measured using 5 items from the emotional abuse subscale that ask questions regarding the frequency of the parents disciplining their children emotionally (eg, “In the last 2 weeks, how often did you shout, yell, or scream at your child in an aggressive manner?”).

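### For the child abuse counts, 90% intervals from 8 schools are too narrow with school-robust SEs, and a plain Poisson mixed model gives no sound model-based fallback

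*Protocol article*

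**What the plan says.** All of this is in the protocol article.

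- **Outcome.** Under Harsh and Abusive Parenting, physical abuse has 4 items and emotional abuse 5. "Each item measures responses on 9-point count scales". Every item covers a two-week window, and its top category, 8, stands for eight or more. The sums therefore run from 0 to 32 and from 0 to 40.
- **Model.** Statistical Methods assigns "Poisson models where outcomes are counts or count distributed". It sets three levels: "repeated measures are nested within individuals, which are, in turn, nested within schools". The component effect is carried by the time interaction: "Level 1 will include a term for categorical time (before and after the intervention) and for the interaction between time and intervention status".
- **Variance.** "Robust SEs will be estimated to adjust for clustering". The article mentions no overdispersion term, occasion-level effect or small-cluster correction.
- **Reporting.** Effects are judged at P<.10 "with 90% CIs. Two-tailed tests will be conducted across all analyses". The same section also says that "all statistical tests will be 2-tailed with α=.05". The intervals for effects are the 90% ones, so 90% is the benchmark here.
- **Size.** Sample Size and Sequence Generation give 8 schools, 4 per site, allocated 1:1:1:1. Each component compares 4 schools with 4. The Abstract reports 151 primary caregivers recruited, about 19 per school (151/8 = 18.9).

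**The concern.** There are two routes to an interval for a component effect on an abuse count, and each has its own weakness.

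1. **The planned route, robust SEs.** A sandwich estimator needs many independent clusters. With 8 schools it is biased downwards and unstable, whatever the outcome distribution.
2. **The obvious retreat, model-based SEs.** A person intercept takes the same value before and after the intervention, so it drops out of the before-after contrast. It absorbs stable differences between parents but not a good or bad fortnight. Several discipline items are summed over the same two weeks, so one stressful fortnight can raise them together. Any such variation above the Poisson level is missing from the model-based SE.

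Intervals that are too narrow turn chance changes in reported abuse into apparent component effects, helpful or harmful. At 75% coverage the false-positive rate is 25% where 10% is intended. Under Intervention Effectiveness, child maltreatment is among the outcomes that inform which components go forward. Limitations concedes low power, which is a different problem: it does not warn that the intervals are too short.

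**Working it through.** The article states no power or variance figure to reproduce, so the benchmark is the nominal 90%.

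**Step 1. Robust SE with 8 schools.** As an approximation, take 8 equal schools and a school-level contrast with 3 parameters (time, time by WhatsApp group, time by in-person sessions), which leaves 8 − 3 = 5 df.

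- The uncorrected sandwich variance is too small by 5/8, so the SE factor is √0.625 = 0.791. The z limit becomes 1.645 × 0.791 = 1.300, and P(|t₅| < 1.300) = 75%.
- With the G/(G−1) factor, the SE factor is √(5/7) = 0.845. The limit is 1.390, and coverage is 78%.
- With that factor and a t₅ limit, 2.015 × 0.845 = 1.703, and coverage is 85%.

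Simulation agrees (8 schools × 20 caregivers, true effect 0, person SD 0.8 on the log scale, counts capped at 32, 6,000 runs per setting). Coverage was 73–75% uncorrected, 76–78% with G/(G−1) and 83.4–84.9% with t₅ added, at every level of overdispersion including none. Smaller full-likelihood runs (400 each) gave 73, 75, 77 and 81%, with a Monte Carlo SE of about 2 points. A third simulation (8 × 19, mean 2.4, 300 runs) gave 69–78% under Poisson and negative binomial alike.

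**Step 2. Model-based SE under Poisson.** Write the occasion-level variance as μ + αμ². The article gives neither μ nor α, so both are assumptions.

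| Assumed α (mean 2.4, 8 × 19, 300 runs) | Poisson | Negative binomial |
|---|---|---|
| 0 | 90% | 89–93% at all four values |
| 0.1 | 85% | |
| 0.5 | 62% | |
| 1.0 | 47% | |

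With α from 0 to 1.0, the Monte Carlo SE is 2 to 3 points. Separate runs gave 79% at α = 0.1, and 69, 61 and 56% at α = 0.25, 0.5 and 1.0.

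The 6,000-run simulation used a log-normal occasion effect, for which α = exp(SD²) − 1.

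| Occasion SD (log) | α | Mean 2 | Mean 5 |
|---|---|---|---|
| 0 | 0 | 89.7% | 91.1% |
| 0.3 | 0.09 | 85.0% | 80.3% |
| 0.5 | 0.28 | 76.4% | 68.5% |
| 0.7 | 0.63 | 66.2% | 58.0% |
| 1.0 | 1.72 | 54.3% | 47.4% |

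Check by hand at mean 5, SD 0.5: the true SD of the estimate is 0.169 and the mean model SE is 0.102. Then 1.645 × 0.102/0.169 = 0.993, and P(|Z| < 0.993) = 68%.

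**Step 3. School-by-time variation.** At mean 5 and occasion SD 0.5, a school-by-time SD of 0.1 or 0.2 lowers Poisson model-based coverage to 61.6 or 48.9%. Negative binomial with z limits also suffers: 85% in one simulation and 82% in another at a school-by-wave SD of 0.15, and 71% at 0.30.

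**Step 4. What a t₅ reference does for the negative binomial.** It widens the interval by 2.015/1.645 = 1.225. Coverage of 85% corresponds to |Z| < 1.440; multiplied by 1.225 this is 1.764, or 92%. By the same step 82% becomes 90%, and 71% becomes 81%. Where z coverage is already 89–93%, it rises to 95–97%, which is conservative.

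**Step 5. School-level analysis.** Regressing each school's log post/pre ratio on the two components, with t on 5 df, covered 89.7–90.5% in every setting of the 6,000-run simulation, including those with school-by-time variation.

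**The case against.** The strongest reply is that Poisson does not make the planned interval fail. The plan calls for robust SEs, and those miss 90% by the same margin under either family. A reader might infer that replacing Poisson with negative binomial cures the problem. It does not: with the sandwich kept, the gain is at most about 10% in empirical SE. This stands, and it is why the change of family has to come with a change in inference.

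A second reply is that the documents show no overdispersion. That also stands as to size. A reader might infer that the abuse scores are known to be strongly overdispersed, but the article gives no mean or variance. At mild dispersion the model-based loss is modest (79–85% at α = 0.1). The robust failure does not depend on this assumption.

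Third, robust SEs could be clustered on persons. They cover 87.5–89.7% if schools do not drift differently over time. At school-by-time SD 0.1 and 0.2 (mean 5, occasion SD 0.5) they fall to 83.8% and 71.4%. The stated purpose is to adjust for clustering, and the randomised unit is the school.

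Fourth, an unseen analysis plan may add dispersion checks or a small-sample correction. It may, but the article itself names the count family and the variance estimator.

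Finally, the stakes are bounded. A reader might take abuse for the main safety or primary outcome. Intervention Effectiveness names positive parenting as the primary proximal outcome and lists child maltreatment among the others. Harms does not use the scores for monitoring, and the effects are described as preliminary.

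**Conclusion.** The point holds for the combination of Poisson family, school-robust SE and 8 schools. The planned 90% interval covers about 70–78%, a result that needs no assumption about the count distribution. Returning to model-based SEs under Poisson is sound only if there is no occasion-level overdispersion and no school-by-time variation. Otherwise coverage falls to about 85, 62 and 47% at assumed α of 0.1, 0.5 and 1.0 (mean 2.4). The mechanism is certain; its size in this trial is not known from the article. Neither change alone is enough: negative binomial with the sandwich kept still undercovers, and small-cluster model-based inference on plain Poisson keeps the variance error. The consequence is a misleading signal on one group of outcomes that feed the component decisions. It does not affect the feasibility objectives.

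**What to change.** In Statistical Methods:

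1. For the abuse scores and other count outcomes, replace Poisson with negative binomial mixed models with the same levels and terms, still reporting rate ratios. A Poisson model with an occasion-level random effect is an equivalent choice.
2. Do not base the 90% CIs of these outcomes on the 8-cluster sandwich SE. Use model-based SEs with a t reference on about 5 df, or take the interval from a school-level regression of the log post/pre ratio on the two components with t on 5 df. The school-level route is the safer one if schools may drift differently over time (Step 4 against Step 5). If site is added to that regression, 8 − 4 = 4 df remain.
3. If the negative binomial model does not converge, fall back to the occasion-level random effect or the school-level analysis, not to plain Poisson.

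The cost is a few sentences, one extra parameter, occasional convergence trouble and wider intervals: a t₅ limit alone is 22.5% wider than z. The school-level route also needs a stated rule for a school total of zero. The article's Results section says that analysis had not yet been performed, so on the article's account the change could still be made before results are seen.

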### Trial Design

This feasibility pilot is a 2×2 factorial cluster randomized trial that compares ParentText (chatbot-led parenting program) delivered to all participants, with different combinations of two engagement components: (1) a WhatsApp support group (yes or no) and (2) either 1 or 2 in-person sessions (Table 1). This study will adopt a parallel design using a 1:1:1:1 allocation ratio (each cluster at each study site exposed to 1 experimental condition).

**Table 1 table1:** Experimental conditions from 2×2 factorial design (n=8 clusters; n=160 families).

Condition	Clusters (schools; n=8), n (%)	Caregivers (primary, n=160; primary and secondary, n=320), n (%)	Children (n=160), n (%)	Facilitators (n=8), n (%)	ParentText	WhatsApp support group (yes or no)	In-person sessions, n
1	2 (25)	40 (25); 80 (25)	40 (25)	2 (25)	On	No	1
2	2 (25)	40 (25); 80 (25)	40 (25)	2 (25)	On	Yes	1
3	2 (25)	40 (25); 80 (25)	40 (25)	2 (25)	On	No	2
4	2 (25)	40 (25); 80 (25)	40 (25)	2 (25)	On	Yes	2

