### Schools

Preschools from the 2 study sites were eligible for inclusion if they had sufficiently sized classes (20-25 children aged 4-6 years/class). Eight preschools were selected from a list of eligible preschools (provided by KEMAS; Multimedia Appendix 1) in Kuala Lumpur and Negeri Sembilan (4 schools per study site). Within each selected preschool, 1 class will be selected (randomly if >1 class) from which 20 families will be invited to participate in the study. Teachers of the selected classes will act as facilitators and contact the families of the children and invite 2 caregivers to participate in the study. Four children in each cluster (ie, 32 in total) will be randomly selected to participate in direct assessments.

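### With 8 schools, robust standard errors under the usual defaults would give nominal 90% intervals that cover about 75–78% for component effects on continuous outcomes

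*Protocol article*

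**What the plan says.** The Trial Design section of the protocol article describes the study this way: "This feasibility pilot is a 2×2 factorial cluster randomized trial". Table 1 is headed "Experimental conditions from 2×2 factorial design (n=8 clusters; n=160 families" and puts 2 schools in each of the 4 conditions. Allocation is by school within site, one school per condition per site. Each component main effect therefore sets 4 schools against 4.

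The Statistical Methods section specifies three-level models in which "repeated measures are nested within individuals, which are, in turn, nested within schools". The effect of interest is carried by a term "for the interaction between time and intervention status", and "level 3 will include terms for the intervention components and the stratifying factor". It then states: "Robust SEs will be estimated to adjust for clustering". Component effects are to be reported two-sided, at P<.10 with 90% confidence intervals.

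The section does not name a sandwich variant, a reference distribution, a degrees-of-freedom method or a small-sample correction. The Limitations section concedes low power but says nothing on whether the intervals are valid.

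**The concern.** A cluster-robust variance is justified as the number of clusters grows. With 8 clusters it is biased downward, because the residuals from which it is built have been shrunk by fitting the model to the same 8 schools. A normal reference also ignores how poorly the variance itself is estimated. Both errors make the interval too short.

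At stake are the objective 5 estimates. The Intervention Effectiveness section uses a judgement on whether a component is effective, alongside cost-effectiveness and feasibility, to decide what goes into the later optimization trial. A component judged both effective and cost-effective is not carried into that trial, so a false positive could escape retesting. The article does not say how effective is to be judged, but these intervals are the only inferential yardstick that it describes.

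**Working it through.** The plan has no sample-size or power figure to reproduce. The figure to check is the nominal 90% coverage.

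**Inputs from the article**
- Schools: G = 8, with 2 per condition (Schools; Table 1).
- Effect terms: time by each component (Statistical Methods). On the scale of school mean change this gives an intercept and two components, so p = 3 parameters and 8 − 3 = 5 residual degrees of freedom. Site is listed as a main effect, so it drops out of change.
- Level: two-sided 90% intervals.

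**Assumptions (not stated in the article)**
- Sandwich variant: uncorrected, or scaled by G/(G−1) = 8/7.
- Reference: normal, multiplier 1.645. Alternatives with t are shown as well.
- Continuous outcome, normal data, equal school sizes. In that case the result does not depend on the intracluster correlation.

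**Formula**

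In the balanced design the component effect is a contrast of 8 school mean changes. Relative to the unbiased variance, the sandwich variance is multiplied by f = (8 − p)/8 = 5/8 if uncorrected, or (8 − p)/7 = 5/7 with G/(G−1). Then

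coverage = P(|t₅| < c × √f),

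where c is the multiplier used.

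| Standard error | √f | c | c × √f | Coverage | Type I error |
|---|---|---|---|---|---|
| Uncorrected | 0.791 | 1.645 (normal) | 1.300 | 75.0% | 25.0% |
| G/(G−1) | 0.845 | 1.645 (normal) | 1.390 | 77.7% | 22.3% |
| Uncorrected | 0.791 | 1.895 (t, 7 df) | 1.498 | 80.6% | 19.4% |
| G/(G−1) | 0.845 | 1.895 (t, 7 df) | 1.601 | 83.0% | 17.0% |
| Bias-corrected | 1 | 1.645 (normal) | 1.645 | 83.9% | 16.1% |
| Bias-corrected | 1 | 1.895 (t, 7 df) | 1.895 | 88.3% | 11.7% |
| Bias-corrected | 1 | 2.015 (t, 5 df) | 2.015 | 90.0% | 10.0% |

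**Width.** The valid interval relative to the default one is 2.015/1.300 = 1.55 (uncorrected) or 2.015/1.390 = 1.45 (G/(G−1)).

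**Simulation, normal reference (uncorrected; G/(G−1))**
- Clustered change scores, intracluster correlation of change 0 to 0.10, 19 caregivers per school (151 recruited primary caregivers / 8 ≈ 19): 74–76%; 77–78%.
- The same with unequal schools of 8–24: 73–74%; 76–77%.
- Three-level model with random intercepts, age and site: 74–76%; 76–78%. In this model a bias-corrected standard error with t on 5 df gave 89–90%.

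**Sensitivity to the model, normal reference**
- One component per model (6 df): 80–82%.
- Adding time by site, or the component-by-component interaction (4 df): 69–72%.
- Adding both (3 df): 61–64%.

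**The case against.** The strongest reply is that the article does not commit to the defaults. It names no sandwich variant, reference or degrees of freedom and leaves the software as Stata or R, and an analysis plan that is not shown might add a correction. That stands against any flat statement that the planned intervals cover 75–78%: the figure is conditional on the defaults. It does not remove the point. The article names robust standard errors as the adjustment for clustering and fixes the interval level, and with 8 schools that adjustment falls short of 90% unless both the bias and the degrees of freedom are corrected.

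A second reply is that this is a feasibility pilot, that objective 5 seeks only preliminary indications, and that Limitations admits low power. This lowers the weight of the point but does not answer it. Low power should show as wide intervals, whereas under-coverage makes them too narrow.

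Three stronger readings are tempting, and the article does not support them.
- A reader might infer that robust errors are the sole guard against overdispersion in the Poisson models, and so fail there. Those models are multilevel, so person and school random effects can absorb extra variation, and count outcomes were not computed.
- A reader might infer that the model leaves out school-level variation in change. The article neither specifies nor excludes such a term, and the present point does not need it.
- A reader might infer that a component is declared effective when P<.10. The article does not define it so.

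**Conclusion.** The point holds in conditional form. If robust standard errors are used with the usual defaults, nominal 90% intervals for a component effect on a continuous outcome cover about 75–78%, and the type I error at P<.10 is about 22–25%. Changing the reference to t on 7 degrees of freedom raises coverage only to about 81–83%. A bias-corrected standard error together with about 5 degrees of freedom restores 90%.

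The exact figure rests on the assumed sandwich variant, the normal reference and the two-component model on change. The direction is more secure: every variant examined that lacked either the bias correction or degrees of freedom suited to the model fell below 90%. Nothing is claimed numerically for Poisson or logistic outcomes. The sentence is wrong as written for 8 schools and should be fixed before analysis. Because objective 5 is preliminary, this is a should-fix matter and not a threat to the feasibility aims.

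**What to change.** Replace the sentence on robust standard errors with small-sample cluster inference.
- **Continuous outcomes:** use Kenward-Roger or Satterthwaite degrees of freedom in the mixed model, or CR2 standard errors with Satterthwaite degrees of freedom. Report t-based 90% intervals.
- **Count and binary outcomes:** keep the multilevel model for the ratio estimates, but base P values and intervals on a t reference with the between-school degrees of freedom (about 5). Add a school-level summary analysis as a check.
- **Randomisation test:** a site-stratified test is at most a sensitivity analysis. Each component has 6 × 6 = 36 allocations, so the attainable two-sided P values for an unadjusted contrast start at 2/36 = 0.056 and then 4/36 = 0.111. At P<.10 the test is therefore conservative.

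The cost is a short rewrite of the analysis text, the added school-level check and standard software options. The Results section says that analysis had not been performed when the article was written, so the change could still be made ahead of the results. The price is intervals about 1.45–1.55 times wider than under the defaults, which is their honest width.
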